# Total neoadjuvant therapy for locally advanced gastric cancer and esophagogastric junction adenocarcinoma: study protocol for a prospective, multicenter, single-arm, phase II clinical trial

**DOI:** 10.1186/s12876-022-02440-5

**Published:** 2022-07-28

**Keywords:** Locally advanced, Gastric cancer, Esophagogastric junction adenocarcinoma, Neoadjuvant chemoradiotherapy, Consolidated chemotherapy

## Abstract

**Background:**

Gastric cancer ranks high in terms of morbidity and mortality worldwide. Multimodal therapy is therefore essential for locally advanced gastric cancer. Recent studies have demonstrated that both perioperative chemotherapy and neoadjuvant chemoradiotherapy can improve the prognosis of patients. However, the completion rate of chemotherapy after surgery remains low, which may affect survival. Thus, identifying the best way to combine radiotherapy, chemotherapy and surgery is important. The aim of this study was to explore the toxicity and efficacy of the total neoadjuvant therapy modality for locally advanced gastric cancer.

**Methods:**

This study will be a prospective, multicenter, single-arm, phase II clinical trial. Patients diagnosed with locally advanced (stage cT3-4 and cN positive, AJCC 8th) gastric cancer and gastroesophageal junction adenocarcinoma will be enrolled. Patients will initially receive radiotherapy (95% planned target volume: 45 Gy/25 f) and concurrent chemotherapy (S-1: 40–60 mg twice a day) followed by six cycles of consolidated chemotherapy (SOX, consisting of S-1 and oxaliplatin) and surgery. The primary objective will assess pathological complete response; the secondary objectives will include toxicities assessing surgical complications, the tumor downstaging rate and the R0 resection rate.

**Discussion:**

Investigation of total neoadjuvant therapy in gastric cancer is limited. The goal of this trial is to explore the efficacy and toxicity of total neoadjuvant therapy for locally advanced gastric cancer and gastroesophageal junction adenocarcinoma.

*Trial registration*: Clinicaltrials.gov (NCT04062058, August 20, 2019).

## Background

In recent years, the morbidity of gastric cancer (GC) has declined worldwide, while the percentage of esophagogastric junction (EGJ) adenocarcinoma has increased rapidly [1]. In China, GC still ranks second in terms of morbidity and mortality [2], with most patients diagnosed at a locally advanced stage. Although radical surgery is the main treatment approach for these patients, the risk of recurrence remains high after surgery [3], and the prognosis is extremely poor. Hence, the combination of radiotherapy, chemotherapy and surgery is essential. Attempts to combine these three important treatment methods remain a research hotspot; in the early years, radiotherapy and chemotherapy were mostly administered after surgery. The INT0116 study enrolled 556 patients diagnosed with GC, all of whom underwent radical surgery. The results showed that compared with surgery alone, adjuvant chemoradiotherapy significantly improved overall survival [4]. Gradually, as D2 resection has become more widespread, the value of adjuvant chemoradiotherapy has been challenged, especially after the results of the ARTIST 2 trial were published [5]. Recently, some phase II or III studies have verified the value of neoadjuvant radiotherapy for locally advanced GC and EGJ cancer in terms of local control and the R0 reaction rate [6, 7]. With advancements in neoadjuvant therapy, the MAGIC, FFCD and FLOT4 trials have confirmed that perioperative chemotherapy will improve patient prognosis [8–10]. Currently, both perioperative chemotherapy and preoperative concurrent chemoradiotherapy are recommended for patients with locally advanced GC according to the National Comprehensive Cancer Network (NCCN) guidelines [11]. However, the completion rate of therapy after surgery is lower than that before surgery, which may influence survival outcomes [12]. Therefore, total neoadjuvant therapy is a promising treatment modality. The POET study is the first phase III clinical trial comparing induced chemotherapy followed by neoadjuvant chemoradiotherapy (NCRT) and surgery with neoadjuvant chemotherapy (NCT). The study ultimately enrolled 119 patients due to slow enrollment. The pathological complete response (pCR) rates for NCRT and NCT were 14.3% and 1.9%, respectively (*P* = 0.03), and the 5-year overall survival rates were 39.5% and 24.4%, respectively (*P* = 0.055) [13]. NCRT showed a tendency to improve survival; however, the dose of radiotherapy was 30 Gy, and the radiotherapy machine and chemotherapy regimen were outdated. Based on the current advancements in intensity-modulated radiotherapy equipment and chemotherapy regimens, our study will assess a newly designed total neoadjuvant therapy comprising NCRT followed by consolidated chemotherapy and surgery for locally advanced GC and EGJ adenocarcinoma. The objective of this trial is to confirm the feasibility and safety of this treatment mode. We aim to provide additional clinical evidence to support the administration of new neoadjuvant treatments.

## Methods

### Study design and objectives

This study will be a single-arm, open-label and multicenter phase II trial. Patients diagnosed with locally advanced (stage cT3-4 and cN positive, AJCC 8th) GC or EGJ adenocarcinoma will be recruited. Before recruitment, each patient will receive gastroscopy, endoscopic ultrasound, and chest-abdomen-pelvis enhanced CT for tumor detection and stages. A multidisciplinary team will screen patients meeting the enrollment conditions. The clinical T stage will be identified by imaging features and laparoscopy information. Metastatic regional nodes will be considered based on their size and biological characteristics. After careful screening, patients will be initially treated with NCRT. The technique of Intensity-Modulated Radiation Therapy (IMRT) or Volumetric Modulated Arc Therapy (VMAT) will be adopted in this trial, with a dose of 45 Gy/25 f to the planned target volume (PTV), and the concurrent chemotherapy will be S-1. Then, the patients will begin six courses of neoadjuvant consolidated chemotherapy (NCCT) using the S-1 and oxaliplatin (SOX) regimen. Finally, patients will undergo surgery after total neoadjuvant therapy. An overview of the study design is shown in Fig. 1.

**Fig. 1 Fig1:**
[figure not shown]
Flow chart. MDT: Multiple Disciplinary Team; NCRT (neoadjuvant chemoradiotherapy): 45 Gy in 25 fractions over 5 weeks concurrently with tegafur; NCCT (neoadjuvant consolidated chemotherapy): is consisted of 6 cycles of SOX regimen. pCR: pathological Complete Response

The primary objective is the assessment of a pathological complete response (pCR), which is defined as no tumor cells in the primary tumor and metastatic regional lymph node. Secondary objectives include assessing toxicities during NCRT and NCCT, surgical complications, the tumor downstaging rate and the R0 resection rate. Recruitment began in November 2019 and is expected to be finished in September 2023. Seven centers in China are participating in this study. The protocol was approved by the institutional ethics committees of these centers and was registered at ClinicalTrials.gov with registration number NCT04062058.

### Eligibility criteria

In this multicenter phase II clinical trial, patients aged 18–70 years with Karnofsky performance status (KPS) ≥ 70; histologically proven gastric cancer or Siewert II/III EGJ adenocarcinoma [14]; and clinical stage T3–4 and N positive without distant metastases were enrolled. No other anticancer treatments were allowed before enrollment. Laboratory investigation requirements were as follows: white blood cell (WBC) count ≥ 3.0 × 10^9^/L, platelet count (PLT) ≥ 100 × 10^9^/L, hemoglobin count (Hb) ≥ 10 g/dl, neutrophil count ≥ 1.5 × 10^9^/L; total bilirubin ≤ 1.5 times the upper limit of normal (ULN); and aspartate aminotransferase (AST) and alanine aminotransferase (ALT) ≤ 1.5 × ULN; serum creatinine (SCr) ≤ 1.0 × ULN; alkaline phosphatase (AKP) ≤ 2.5 × ULN. Patients agreed to sign an informed consent form before enrollment.

The exclusion criteria included patients aged more than 70 years or less than 18 years, prior anticancer treatment, pregnant or lactating females, metastatic disease, history of myocardial infarction or cerebral infarction within the past 6 months, active infections of tuberculosis or hepatitis, and refusal to provide informed consent.

### Treatment

Total NCRT will involve NCRT followed by six cycles of consolidated chemotherapy and surgery.

#### Neoadjuvant chemoradiotherapy

Before the simulation, patients will be instructed to fast for at least 4 h and drink 300 ml semifluid diet 10 min before CT (4DCT) simulation and daily radiotherapy to maintain a consistent stomach volume. The patients will lie on the table in the supine position with their arms crossed above their heads and will be stabilized by a thermoplastic mask under free-breathing conditions. CT scanning will be performed from the clavicle to the fifth lumbar spine, with a scanning thickness of 0.5 cm. IMRT or VMAT will be recommended during radiotherapy. The 45 Gy dose of radiotherapy will be delivered in 25 fractions. Concurrent chemotherapy is S-1 administered at a dose of 40 to 60 mg twice daily according to body surface area (BSA) (Table 1).

**Table 1 Tab1:** Dose of S-1

BSA (m^2^)	Dose
< 1.25 m^2^	40 mg bid
1.25—1.5 m^2^	50 mg bid
≥ 1.5 m^2^	60 mg bid

Based on the EORTC-ROG expert opinion and third edition of the Japan Gastric Cancer Association guideline [15, 16], the radiation field will include the gross tumor, metastatic regional nodes and elective regional lymph node stations. The gross tumor volume (GTV) will be defined as a primary tumor determined by available technology. The diagnosis of metastatic regional lymph nodes will require comprehensive judgment based on their size and morphology. For example, for metastatic regional lymph nodes, the short axis diameter of the lymph nodes should be larger than 8 mm; a rounded shape, necrosis in the center of the lymph node, and clustered lymph nodes should be observed; marked enhancement should be identified during enhanced CT; and lymph nodes should be enlarged significantly during the examination. A metastatic regional lymph node will be defined as a metastatic regional node (GTVnd). The clinical target volume (CTV) contains GTV, GTVnd and elective regional lymph node stations according to the location of the tumor (Table 2).

**Table 2 Tab2:** Elective lymph node station according to tumor location

Tumor location	Elective lymph node stations
EGJ (Siewert II)	1, 2, 3, 4sa, 7, 9, 11p, 19, 20, 110, 111
EGJ (Siewert III)	1, 2, 3, 4sa, 7, 9, 10, 11p, 11d, 19, 20, 110, 111
GC (proximal third)	1, 2, 3, 4sa, 4sb, 7, 9, 10, 11p, 11d, 19
GC (middle third)	1, 2, 3, 4sa, 4sb, 4d, 7, 8, 9, 10, 11p, 11d, 18, 19
GC (distal third)	3, 4d, 5, 6, 7, 8, 9, 11p, 11d, 12, 13, 17, 18

Referring to the ICRU-62 report [17], the planned target volume will be derived from CTV plus 1 cm in the cranio-caudal direction and 0.5 to 0.7 cm in the anterior–posterior and left–right directions. The dose limitations of the organs at risk (OARs) will be as follows: Dmax stomach ≤ 50 Gy, V30 liver < 26%, V20 kidney < 26%, Dmean kidney < 18 Gy, Dmax spinal cord PRV ≤ 40 Gy, V10 bone marrow < 26%, Dmax intestine ≤ 42 Gy, and V40 intestine < 10% (for EGJ cancer, heart and lung should be included, V30 heart < 26%, and V20 lung < 20%).

Cone beam computed tomography (CBCT) scans will be performed daily during the first week and then once a week at least based on the clinical situation. Routine blood tests will be monitored weekly, and biochemical tests will be performed every two weeks during NCRT. Patients will take a 3-week break, and then a physical examination will be conducted before NCCT. The contents of the examination are shown in Table 3.

**Table 3 Tab3:** Assessment and intervention schedule for the trial

	Screening	During NCRT	Before NCT	During NCT	Before surgery	Follow-up		
						Year 1-2: every 3 months	Year 3-5: every 6 months	> 5 year: every 1 year
Physical examination	√	X	√	X	√	√	√	√
Blood routine	√	X	√	X	√	√	√	√
Urine routine	√				√			
Stool routine	√				√			
Biochemical test	√	△	√	△	√	√	√	√
CEA	√		√	○	√	√	√	√
CA199	√		√	○	√	√	√	√
CA724	√		√	○	√	√	√	√
Electrocardiogram	√				√			
Enhanced CT*	√		√	○	√	√	√	√
Ultrasound**	√		√	○	√	√	√	√
Gastroscopy	√				√	√	√	√
Endoscopic ultrasound	√				√			
Pathology	√							

√: once, X: weekly, △: biweekly, ○: every 3 cycles

*scanning range: chest, abdomen and pelvis

**scanning range: neck and supraclavicular

#### Neoadjuvant consolidated chemotherapy

The NCCT regimen will involve six cycles of SOX, with each cycle lasting for 21 days. Oxaliplatin will be delivered intravenously at a dose of 130 mg/m2 on day 1, and S-1 will be given orally at a dosage of 40 to 60 mg twice daily according to BSA (Table 1) on days 1 to 14. Patients will take a seven-day break after 14 days of chemotherapy, and complete physical examination will be performed every 3 cycles.

#### Surgery

Standard radical surgery will be performed 6 weeks after the last cycle of chemotherapy. For the type of resection, laparoscopic will be recommended. For the Siewert II EGJ, laparoscopy can also be combined with thoracoscopy. For the proximal GC and EGJ, esophagectomy and total or subtotal gastrectomy will be recommended. For the middle or distal GC, subtotal gastrectomy will be recommended. For the gastrointestinal tract reconstruction, Billroth I or Billroth II reconstruction will be used for subtotal gastrectomy and Roux-en-Y reconstruction will be used for total gastrectomy. D2 resection will be recommended. The definition of D2 lymph node dissection can be referred to NCCN guidelines [11]. At least 16 or greater lymph nodes are required to examine during the surgery. If the disease progresses during neoadjuvant therapy, a multiple disciplinary team (MDT) will be required to discuss the subsequent treatment.

### Tumor response and toxicity criteria

The contents of the tumor efficacy assessments during therapy and follow-up are listed in Table 3. Response Evaluation Criteria in Solid Tumors (RECIST) version 1.1 guidelines will be adopted as the tumor response evaluation criteria [18]. Toxicities occurring during therapy will be assessed based on Common Terminology Criteria of Adverse Events (CTCAE) version 3.0. It will be necessary to reduce the dose or to stop treatment when serious adverse effects occur. During neoadjuvant or concurrent chemotherapy, when grade III gastrointestinal, neurotoxic or grade IV leukopenia occurs without recovery within 5 days after treatment, the dose will be reduced to 80% of the original dose. Chemotherapy will be stopped if any grade IV adverse effects occur except leukopenia. Radiotherapy will be stopped if a patient does not recover in 7 days when grade III gastrointestinal occurs after treatment. Any grade IV adverse effect except leukopenia will result in termination of radiotherapy. When a patient recovers to grade 0-I, radiotherapy may continue without receiving concurrent chemotherapy. It will be unnecessary to adjust the radiation dose. Surgical complications will be defined as anastomotic leakage, anastomotic bleeding or abdominal infection and others within 30 days after surgery. Tumor pathological response will be assessed by using the tumor response grading (TRG) system proposed by Mandard et al. [19]. All adverse events will be recorded in a case report form (CRF). Adverse events will be reported to the ethical institution committee within 24 h and dealt with immediately.

### Sample size calculation

The primary objective is to determine the pCR rate in this trial. According to the results of the prospective phase II trial previously conducted at our center [20], the pCR rate of patients who received NCT was 14% (P0). We assume that after NCRT and six cycles of NCCT, the pCR rate will reach 28% in this study. Taking into consideration the loss of patients and the optimal two-stage design of phase II clinical trials, the test level α is 0.05 with a power of 80%. The required sample size of the study will be 82 patients. After 33 patients are enrolled, a planning interim analysis will be conducted. If the number of patients who received pCR is less than five, the study will be closed.

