### Statistical analysis

For descriptive statistics, categorical variables are described by frequency, rate, or 95% confidence interval. Continuous variables are described by the mean, median, quartile or standard deviation. For comparisons between groups, categorical variables will be compared by using the chi-square test or Fisher’s exact test. For continuous variables, the paired *t* test or Wilcoxon test will be used to compare changes between baseline and endpoint. The Kaplan–Meier method will be used to predict overall survival probabilities at specific time points. All statistical tests will be two-sided. The level of significance will be set to *P* < 0.05.

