Perioperative therapy has advanced rapidly, and 6–8 cycles of perioperative chemotherapy are currently recommended according to the NCCN guidelines [11]. In the MAGIC study, six cycles of an ECF/ECX (stepirubicin, cisplatin and fluorouracil or capecitabine) regimen were used before and after surgery; although overall survival improved, only 41.6% of the patients completed the planned six cycles [9]. In the FLOT4 study, only 46% of patients completed all perioperative treatments [8]. In the CRITICS trial, the completion rate of adjuvant chemotherapy and chemoradiotherapy was 60% [12]. As mentioned above, the complete percentage of adjuvant therapy was quite low. Hence, in this trial, all perioperative treatment was administered before surgery. Moreover, preoperative chemotherapy may reduce the surgery rate for potential distant metastasis patients. In recent years, an increasing number of investigators have focused on the use of a total neoadjuvant therapy modality in patients with gastrointestinal tumors, especially those with rectal cancer [31], yet similar studies on GC are quite limited. Kim et al. explored the induction of NCT followed by NCRT for GC patients; adjuvant chemotherapy was needed for patients whose tumors were not downstaged to stage 0 to I after surgery. A total of 42 patients were enrolled in their study; 33.3% were pathologically downstaged to stage 0-I after preoperative treatment, and the 3-year overall survival rate was 75.5% [23]. The results of the use of total neoadjuvant therapy approaches for GC and EGJ adenocarcinoma phase II clinical trials were published at the 2019 ASTRO (American Society for Therapeutic Radiology and Oncology) meeting. Patients received 8 cycles of induction chemotherapy (FOLFIRINOX: Oxaliplatin, Irinotecan, Fluorouracil and leucovorin) followed by NCRT and surgery. Of the 25 patients enrolled in this trial, 20 underwent surgery, and the pCR rate was 35%. The results of this trial demonstrated the promising effects of total neoadjuvant therapy [32]. To further improve the downstaging rate, we prolonged the interval time between radiotherapy and surgery. The strategy of receiving NCRT followed by NCCT and surgery is rarely reported for GC.

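### The claimed allowance for patient loss and the stated 80% power do not fit the 33/82 design, which is the uninflated optimal two-stage design at 90% power

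*Protocol article*

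**What the plan says.** The protocol article, under Sample size calculation, takes 14% as the null pCR rate and assumes that "the pCR rate will reach 28% in this study". The error level and power are given as "the test level α is 0.05 with a power of 80" per cent. The total is introduced with "Taking into consideration the loss of patients and the optimal two-stage design of phase II clinical trials" and stated as "The required sample size of the study will be 82 patients". The interim look comes after 33 enrolled patients, and the study closes if fewer than five have a pCR.

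The section gives no loss rate, no size before inflation and no final success threshold. Under Statistical analysis the general statement is "All statistical tests will be two-sided".

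Two other places show that some patients may have no specimen to assess. Under Surgery: "If the disease progresses during neoadjuvant therapy, a multiple disciplinary team (MDT) will be required to discuss the subsequent treatment". The Discussion describes an earlier total neoadjuvant series: "Of the 25 patients enrolled in this trial, 20 underwent surgery, and the pCR rate was 35" per cent.

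**The concern.** A sample size said to allow for loss should exceed the bare design size by a traceable amount. Here both stage sizes coincide with a bare design, and that design has a different power from the one stated. The allowance and the power therefore cannot both be read off the numbers.

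This matters more for pCR than for most endpoints. A pCR needs a resected specimen, and a patient who progresses or never reaches surgery is usually a treatment failure. An allowance for loss normally replaces patients who leave the analysis. If unresected patients were treated that way, the remaining denominator would favour the regimen when set against a fixed 14%. If they are instead counted as failures, and 28% was meant for resected patients, the trial has less power than its sizes suggest.

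**Working it through.** **Inputs.** From Sample size calculation: p0 = 0.14, p1 = 0.28, alpha 0.05, power 80%, n1 = 33, N = 82, closure below five pCR (so r1 = 4). Loss rates are assumptions, because the article gives none. The 20% scenario is the unresected share in the cited series, 5/25.

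**Formula.** For a design r1/n1, r/n, the exact probability of declaring success at rate p is the sum over x from r1 + 1 to n1 of b(x; n1, p) × P(Y > r − x), with Y ~ Bin(n − n1, p). The optimal design minimises the expected sample size at p0, subject to the alpha and power limits.

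**Step 1: reproduce 33/82.**

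| Target | Optimal design (r1/n1, r/n) | Alpha | Power |
|---|---|---|---|
| One-sided 0.05, 80% | 3/20, 13/65 | 0.0476 | 0.803 |
| One-sided 0.025, 80% | 4/25, 16/76 | 0.0250 | 0.808 |
| One-sided 0.05, 90% | 5/33, 16/82 | 0.0498 | 0.901 |

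The stated 80% does not reproduce 33/82 at either one-sided level. The 90% design matches both sizes with no inflation. A real 10% allowance on that design would need 82/0.9 = 91.1, so 92 patients.

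**Step 2: could 82 be an inflated 80% design?** 65/0.8 = 81.25, which rounds up to 82, so the total alone can be reached with a 20% allowance. The first stage would then be 20, or 20/0.8 = 25 if also inflated. Neither is 33.

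**Step 3: the interim rule.** The 5/33 design closes at five or fewer pCR; the article closes below five. With r1 = 4 and N = 82, a final cut of 16 (17 or more for success) gives alpha 0.056 and power 0.932. A final cut of 17 gives alpha 0.032 and power 0.901.

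**Step 4: unresected patients counted as non-pCR, with 28% holding only among resected patients.** The effective rate is 0.28 × (1 − d).

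| Unresected d | r1 = 5, r = 16 | r1 = 4, r = 16 | r1 = 4, r = 17 |
|---|---|---|---|
| 0% | 0.901 | 0.932 | 0.901 |
| 5% | 0.854 | 0.891 | 0.846 |
| 10% | 0.790 | 0.833 | 0.771 |
| 15% | 0.709 | 0.755 | 0.676 |
| 20% | 0.610 | 0.656 | 0.565 |

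If 28% is already a rate per enrolled patient, the 0% row applies whatever the unresected share.

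**Step 5: unresected patients dropped.** Both stages are shrunk in proportion, with r1 = 4 and the final cut chosen to keep alpha below 0.05. At 10% loss (30/74, cut 15) power is 0.888. At 20% loss (26/66, cut 14) it is 0.807. The estimate shifts, however: a true 14% per enrolled patient appears as 0.14/0.9 = 15.6% or 0.14/0.8 = 17.5%.

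**Step 6: the cited series.** 35% of 25 is 8.75, not a whole number, whereas 35% of 20 is 7. The rate is therefore among resected patients, and per enrolled patient it is 7/25 = 28%. The choice of denominator moves the result by 7 points, half of the 14-point difference sought.

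**The case against.** The strongest reply is that 82 is the uninflated size only at a power the article does not state. On the stated 80% the base is 65, so 82 holds 17 spare patients, numerically a 20% allowance. That is correct for the total, but it leaves the first stage of 33 unexplained. The match of both sizes is strong inference about how the numbers arose, not proof.

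The second reply is that losses do not clearly take power below the stated 80%. This largely stands. Erosion starts from about 90%, and an analysis of evaluable patients only still has about 81% at 20% loss. With the article's own interim rule and a final cut of 16, power is 83% at 10% unresected, although alpha is then 0.056.

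The third is that the article nowhere says unresected patients will be left out, and analysis populations are commonly set in the full protocol or SAP. That stands too. A reader might infer from the loss clause that exclusion is planned and that the false-positive rate therefore rises to about 14%: the 26/66 design with cuts 4 and 14 succeeds with probability 0.145 at a true resected rate of 17.5%. The documents do not support this. It needs exclusion, 20% unresected, a null rate per enrolled patient, and thresholds that are not in the article. If the 14% was itself a resected-only rate, a resected-only comparison would be like for like.

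**Conclusion.** The sample size statement is wrong as written. The stated 80% power, the sizes 33 and 82, the closure rule and the claimed loss allowance do not belong to one design. Very probably no allowance was added and the sizes come from a 90% power calculation. It would go too far to say that the allowance certainly does not exist, since the total alone can be reached by inflating 65.

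The consequence of losses is conditional. With a final cut of 16, counting unresected patients as failures gives 79% (r1 = 5) or 83% (r1 = 4) power at 10% unresected and 61% or 66% at 20%, but only if 28% is a rate among resected patients. Dropping them leaves power at about 81% at 20% loss but biases the pCR rate upward, to 17.5% for a true 14%, if the null is per enrolled patient. All loss rates and the final cuts are assumptions, and the article does not say on which basis 14% and 28% are defined.

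**What to change.** 1. Delete the loss clause, or state the base size and the loss rate behind it.
2. Restate the power to match 33/82, about 90% with no loss, together with the one-sided alpha and the final threshold.
3. Reconcile the interim rule with that design. The matching design closes at five or fewer pCR with a final cut of 16. Keeping closure below five with a final cut of 17 gives alpha 0.032 and power 0.901.
4. State that all enrolled patients form the denominator at both looks, with no resection or no pathology counted as no pCR, and that 14% and 28% are on that basis. If the source of the 14% used resected patients only, convert it first.
5. Report the pCR rate among resected patients as secondary.

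The cost is a change of wording and a somewhat lower headline pCR rate than a resected-only figure would give. No extra patients are needed.

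### The sizes 33 and 82 are the optimal two-stage design for 90% power, not the stated 80%; the loss clause does not explain the gap, and the printed interim rule is not that design's

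*Protocol article*

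**What the plan says.** All inputs except a loss rate stand in the protocol article, Methods, Sample size calculation:

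- Null rate: "the pCR rate of patients who received NCT was 14% (P0").
- Target rate: "the pCR rate will reach 28% in this study".
- Design: "the optimal two-stage design of phase II clinical trials".
- Error rates: "the test level α is 0.05 with a power of 80" per cent. Sidedness is not given here; the Statistical analysis section says "All statistical tests will be two-sided".
- Loss: "Taking into consideration the loss of patients", with no rate and no number before inflation.
- Sizes: "The required sample size of the study will be 82 patients" and "After 33 patients are enrolled, a planning interim analysis will be conducted".
- Interim rule: the study closes if fewer than five patients have a pCR, that is, at 4 or fewer of 33.

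No final cut-off is printed.

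**The concern.** This paragraph is the only justification for the trial's size and for its interim look on the primary endpoint. Its rates, alpha, power and design type fix the two stage sizes, so the statement can be checked against itself. If the printed power belongs to another design, three things follow. A reader of a negative result will take the wrong chance of missing a true 28%. A reader who repeats the calculation will not get 82. And it becomes unclear whether the loss allowance that the text claims is in the number at all. The interim rule depends on the same design, so a mismatch there affects the type I error.

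**Working it through.** **Method.** For stage 1 size n1, interim boundary r1 (close at r1 or fewer), total n and final boundary r (success above r), the probability of declaring success at true rate p is

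R(p) = Σ over x from r1+1 to n1 of Bin(x; n1, p) × P[Bin(n − n1, p) > r − x].

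Alpha is R(0.14) and power is R(0.28). The expected size under the null is EN0 = n1 + (1 − PET0)(n − n1), where PET0 = P[Bin(n1, 0.14) ≤ r1]. The optimal design has the smallest EN0 among all designs that meet the alpha and power limits.

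**Step 1: the stated inputs.** Exhaustive search, P0 = 0.14, P1 = 0.28:

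| One-sided alpha limit | Power target | Optimal r1/n1, r/n | Alpha | Power |
|---|---|---|---|---|
| 0.05 | 0.80 | 3/20, 13/65 | 0.0476 | 0.8035 |
| 0.05 | 0.85 | 4/27, 14/69 | 0.0440 | 0.8514 |
| 0.05 | 0.90 | **5/33, 16/82** | 0.0498 | 0.9006 |
| 0.025 | 0.80 | 4/25, 16/76 | 0.0250 | 0.8075 |
| 0.025 | 0.90 | 7/41, 21/105 | 0.0250 | 0.9001 |

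For 3/20, 13/65, PET0 = 0.6959 and EN0 = 20 + 0.3041 × 45 = 33.7. For 5/33, 16/82, PET0 = 0.6878 and EN0 = 33 + 0.3122 × 49 = 48.3. The minimax design at 0.05 and 80% is 5/35, 11/51. Only the 90% optimal design at one-sided 0.05 gives both 33 and 82. Reading alpha as two-sided (0.025 in one tail) does not give them.

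The Discussion reports 14.3% and 11.1% for the two arms of the earlier trial. Used as P0 with P1 = 28% and 80% power, they give optimal sizes of 22/57 and 16/38, so they do not explain 33 and 82 either.

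**Step 2: can loss explain it?** The rate is not stated, so it is an assumption.

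- At 20% loss, 65/(1 − 0.20) = 81.25, rounded up to 82.
- At the same 20%, 20/(1 − 0.20) = 25, not 33.
- The rate needed for 65 to become 82 is 1 − 65/82 = 21%; for 20 to become 33 it is 1 − 20/33 = 39%.

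No single rate gives both sizes. If 33 and 82 come from the 90% design, they contain no loss allowance.

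**Step 3: power under the printed interim rule.** All 82 evaluable:

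| Close at | Success at | Alpha | Power |
|---|---|---|---|
| ≤ 5 of 33 (90% design) | ≥ 17 of 82 | 0.0498 | 0.9006 |
| ≤ 4 of 33 (as printed) | ≥ 17 of 82 | 0.0563 | 0.9319 |
| ≤ 4 of 33 (as printed) | ≥ 18 of 82 | 0.0316 | 0.9007 |

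The printed rule with the 90% design's own final cut-off exceeds 0.05.

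**Step 4: power if lost patients count as non-pCR.** Assume 10% loss. The effective target rate is 0.28 × 0.90 = 0.252. With closure at 4 or fewer, R(0.252) = 0.833 for success at 17 or more and 0.771 for 18 or more. At an assumed 5% (0.28 × 0.95 = 0.266) they are 0.891 and 0.846.

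**The case against.** The best defence is the loss clause. It stands directly before the error rates, and 82 on its own equals 65 inflated for 20% loss. The argument can go further and treat 33 and 82 as enrolled patients. If 20% are lost and excluded, about 26 and 66 remain (33 × 0.8 = 26.4; 82 × 0.8 = 65.6). Closing at 4 or fewer and requiring 15 or more successes then gives alpha 0.031 and power 0.807, so 80% may well be reached after loss. That much stands: 82 cannot be called wrong, and a reader who infers that the trial enrols 82 − 65 = 17 patients too many goes beyond the text. It does not rescue the statement, because 26 and 66 are not the optimal design for these inputs, and the loss rate, the exclusion of lost patients and the final cut-off are all assumed by this argument and not given in the protocol.

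A reader might also infer that the protocol as written has 90.1% power and a 1-in-10 chance of missing a true 28%. The documents do not support that without conditions. The 0.9006 belongs to closure at 5 or fewer, which is not the printed rule, and to full evaluability, although the text expects loss.

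Finally, the error is on the safe side: with all patients evaluable the trial has more power than it claims, and the power label itself does not raise the false-positive risk. That stands and limits the severity.

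**Conclusion.** The point holds. The stated 80% power and the stated sizes do not belong to the same optimal two-stage design: 80% gives 20 and 65, while 33 and 82 match the 90% design in both stages. The match on both sizes makes a misprinted power the likeliest explanation, but the document does not prove it.

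With all 82 evaluable and the printed interim rule, power is 0.90 to 0.93 depending on the final cut-off, 10 to 13 points above the stated figure. The upper value costs an alpha of 0.056. With an assumed 10% loss counted as non-pCR, power is about 0.77 to 0.83, so the surplus disappears. The document does not support calling the trial underpowered, or 82 too large.

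Severity is moderate: at full evaluability the error understates power, but the power, the loss allowance and the interim boundary cannot all be read as one optimal design.

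**What to change.** 1. Keep 33 and 82. State the power as about 90% with all patients evaluable, at one-sided alpha 0.05, and exempt this test from the general two-sided statement in the Statistical analysis section.
2. Either give the assumed loss rate, the numbers before inflation and how lost patients are counted, with the power that results, or delete the claim that loss was taken into account.
3. Reconcile the printed interim boundary (fewer than five) with that of the 33/82 design (5 or fewer), and print a final cut-off that holds alpha at or below 0.05 for the boundary kept. If the printed boundary is kept, that means success at 18 or more of 82 (alpha 0.032, power 0.901). If the design's boundary is adopted, it means 17 or more (alpha 0.0498, power 0.9006).

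Items 1 and 2 are wording and do not change enrolment. Item 3 clarifies or changes a decision rule: under the printed rule a result of exactly 5 of 33 continues, and under the design's rule it stops. Recruitment began in November 2019, so the interim may already have been reached. The amendment should say whether it had been, and whether the pCR count was known when the boundary was settled.
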